## Abstract

**Introduction:**

Up to 80% of patients with respiratory tract infections (RTI) attending healthcare facilities in rural areas of China are prescribed antibiotics, many of which are unnecessary. Since 2009, China has implemented several policies to try to reduce inappropriate antibiotic use; however, antibiotic prescribing remains high in rural health facilities.

**Methods and analysis:**

A cluster randomised controlled trial will be carried out to estimate the effectiveness and cost effectiveness of a complex intervention in reducing antibiotic prescribing at township health centres in Anhui Province, China. 40 Township health centres will be randomised at a 1:1 ratio to the intervention or usual care arms. In the intervention group, practitioners will receive an intervention comprising: (1) training to support appropriate antibiotic prescribing for RTI, (2) a computer-based treatment decision support system, (3) virtual peer support, (4) a leaflet for patients and (5) a letter of commitment to optimise antibiotic use to display in their clinic. The primary outcome is the percentage of antibiotics (intravenous and oral) prescribed for RTI patients. Secondary outcomes include patient symptom severity and duration, recovery status, satisfaction, antibiotic consumption. A full economic evaluation will be conducted within the trial period. Costs and savings for both clinics and patients will be considered and quality of life will be measured by EuroQoL (EQ-5D-5L). A qualitative process evaluation will explore practitioner and patient views and experiences of trial processes, intervention fidelity and acceptability, and barriers and facilitators to implementation.

**Ethics and dissemination:**

Ethical approval was obtained from the Biomedical Research Ethics Committee of Anhui Medical University (Ref: 20180259); the study has undergone due diligence checks and is registered at the University of Bristol (Ref: 2020-3137). Research findings will be disseminated to stakeholders through conferences and peer-reviewed journals in China, the UK and internationally.

**Trial registration number:**

ISRCTN30652037.

Strengths and limitations of this studyThis is a large cluster randomised trial to determine whether the intervention is effective in reducing antibiotic prescribing for patients with respiratory tract infection in township health centres compared with usual care.This study will also evaluate the cost-effectiveness of an intervention to reduce antibiotic prescribing in rural areas.The quantitative and qualitative research in the trial could also provide recommendations on how to reduce antibiotics prescribing at village clinic level.The use of direct observation will ensure accurate assessment of antibiotic prescribing in both baseline and intervention phases.The study, though selected to be representative of rural populations in China, includes 10 counties from 4 regions across the Anhui Province, which may have limited generalisability.

## Introduction

Antimicrobial resistance (AMR) specifically refers to the evolution of drug-resistant micro-organisms, including bacteria, which is driven by high rates of antibiotic use and is a pressing problem for global health and development.^1–3^ If resistance continues to increase, common bacterial infections will eventually become untreatable.^4 5^

Since 2009, China has implemented the national essential medicines scheme and zero-mark-up policies to try to reduce inappropriate antibiotic use.^6 7^ In 2012, the Chinese Ministry of Health issued a regulation to limit antibiotic prescribing to 20% of outpatient prescriptions in all patients.^8^ However, the antibiotic prescribing rate in healthcare facilities in less developed or rural areas remains as high as 80%.^9–14^

In China, patients can choose to go to the outpatient department of any health facility without a referral letter,^15^ however, rural residents mainly seek healthcare from township health centres or village clinics, the two lowest-level health facilities in China’s rural healthcare system. If patients develop severe symptoms, they are more likely to go directly to the outpatient clinic in the county hospital.^15 16^ Many patients attend village clinics and township health centres with respiratory tract infections (RTIs) such as common cold, sore throat, and acute bronchitis and are frequently prescribed antibiotics even though most cases are likely to be viral and antibiotics are therefore unnecessary^17–20^ Our previous study found that the antibiotic prescribing rate for RTI patients was up to 85% in rural Anhui Province.^21^ In addition to the implications for AMR, there is a cost to patients^22 23^ for extra health resource utilisation (consultation fees, medication costs, loss of productivity costs), most of which would not be reimbursed through national medical insurance schemes. Therefore, reducing antibiotic prescribing in village clinics and township health centres is likely to be both safe and economically beneficial to patients. Since the start of the COVID-19 pandemic, village clinics have periodically been prohibited from providing treatment to RTI patients; therefore, this trial focuses on provision of care in township health centres.

Township health centres in China are staffed with both qualified doctors and some health practitioners who are usually referred to as ‘village practitioners’ but would not have a degree in medicine. Village practitioners are required to undergo basic training in healthcare provided by the local healthcare authority issued with a medical practice licence. Antibiotic prescribing in township health centres is influenced by uncertainty about which RTI need antibiotics and by widespread beliefs that common infections should be treated with antibiotics.^15^ Practitioners are also concerned about losing patients and believe that prescribing antibiotics helps maintain good relationships with their patients. Public campaigns on antimicrobial stewardship (AMS)^23–25^ are very limited in rural areas and there is little technical support for village and township practitioners from senior clinical consultants and healthcare authorities, which makes it difficult for them to change norms of high antibiotic use.

This study will aim to determine whether the intervention safely reduces antibiotic prescribing for patients with RTI in township health centres. The study will provide evidence of effectiveness, value for money and barriers and facilitators to implementation that can inform policy and clinical practice. If pandemic conditions permit, the study will also pilot implementation of the same intervention in a limited number of village clinics to demonstrate proof of concept in lower level health facilities.

## Methods and analysis

### Aims and objectives

This study aims to evaluate the effectiveness of a complex intervention aimed at healthcare practitioners and patients at township health centres, to reduce antibiotic prescribing for RTIs compared with usual care in township health centres.

The primary outcome will be the percentage of antibiotics (intravenous and oral) prescribed for RTI patients.

Secondary objectives are to:

Estimate the cost-effectiveness of the intervention and the cost implications for both township health centres and patients.Evaluate the impact of reduced antibiotic use on patient satisfaction with care.Evaluate the impact of reduced antibiotic use on patient symptom severity, duration and recovery rates.Investigate patient antibiotic consumption rates (prescribed or obtained from another source).Understand practitioner and patient views of the intervention and barriers and facilitators to implementation.

### Trial design

This is a pragmatic, two-armed (intervention vs usual care) trial with an embedded cost-effectiveness and qualitative evaluations, with randomisation at township health centre level, using observed antibiotic prescribing to assess effectiveness.

### Participants and recruitment procedures

### Selection of township health centres

We originally started the trial recruitment at village clinic level. However, in May 2021, there was a small local COVID-19 outbreak in Anhui Province, since when village clinics have not been allowed to treat RTI patients in Anhui and our trial recruitment had to be postponed. Currently, patients with suspected COVID-19 symptoms (specifically patients with a temperature of more than 37.3°) must be referred to specialist COVID-19 clinics or specialist COVID-19 hospitals for treatment. We did some preliminary fieldwork in June 2021 and found it is still very difficult to recruit RTI patients at village clinic level and the research team assessed that this situation may not change within the next 12 months. However, we found that township health centres are still able to treat RTI patients regularly. In order to complete recruitment and maintain trial feasibility, we therefore decide to change the recruitment sites from village clinics to township health centres.

We will recruit 40 township health centres from 10 counties (4 township health centres per county), those counties will be randomly selected from 4 regions geographically dispersed across Anhui Province. We will randomly recruit 6 counties from two regions in densely populated North Anhui and four counties from another two regions from sparsely populated South Anhui. We will seek support from local county health authorities during the recruitment of township health centres. They will provide a list of townships in their area and the research team will randomly select four township health centres. Local county health authorities will screen the selected townships and may exclude selected townships, for which a reason will be recorded.

### Recruitment of practitioners

The recruitment of health practitioners will be fair. Once a township health centre is recruited and has given permission for its staff to participate, all the practitioners working in the recruited township health centres will be invited to participate in the study. Once practitioners are identified and recruited, informed consent (online supplemental appendix 1) will be obtained immediately.

10.1136/bmjopen-2020-048267.supp1Supplementary data

Exclusion criteria

Practitioners who do not have basic computer skills.Practitioners who are not involved in clinical diagnosis and medicine prescribing.

The background information of participating township health centres and practitioners will be collected. A senior practitioner in the recruited township health centre will complete a clinic background information questionnaire (online supplemental appendix 2); and all practitioners working in the clinic will give their demographic data in a practitioner background information questionnaire (online supplemental appendix 3).

10.1136/bmjopen-2020-048267.supp2Supplementary data

10.1136/bmjopen-2020-048267.supp3Supplementary data

A baseline audit of 400 RTI patients across the 40 township health centres will be conducted (10 RTI patients for each township health centre). This baseline audit will only collect primary outcome data, including the antibiotic prescribing rates at each clinic. Then all the township health centres will be randomised at a 1:1 ratio to usual care group versus intervention group, using the baseline antibiotic prescribing rates to balance high and low prescribing clinics between the arms. Each group will have 20 township health centres (details see figure 1).

**Figure 1 F1:**
[figure not shown]
Trial flow chart. RTI, respiratory tract infection.

### Recruitment of patients

All patients with RTIs who seek healthcare from the recruited health centres will be screened for eligibility and invited to participate in this study. Researchers from Anhui Medical University will undertake patient recruitment on-site until 30 participants have been recruited at each township health centre. Informed consent (online supplemental appendix 4) will be obtained from all the patients who agree to participate in this study.

10.1136/bmjopen-2020-048267.supp4Supplementary data

Currently, patients with suspected COVID-19 symptoms must be referred to specialist hospitals and township health centres are not expected to see suspected COVID-19 patients who present for treatment. However, some of these patients test negative for COVID-19 and are then referred back to their local clinic for treatment for their non-Covid RTI. These patients will be eligible for inclusion in our study.

#### Eligibility Criteria

##### Inclusion criteria

Adult (aged ≥18 years old).Patient who is diagnosed with an RTIs in the recruitment consultation: blocked/runny nose, coughing with or without sputum, dry/sore throat, breathing problems, fever, ear inflammation (blocked ear, tinnitus, ear discharges, earache).

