##### Exclusion criteria

Patients who have previously sought treatment for this illness from a normal clinic (not a specialist COVID-19 clinic).Patients who are unable to provide fully informed consent (eg, dementia, psychosis or severe depression).Patients who are pregnant.

Patients without bacterial infections, immunocompromised patients and patients with non-infective conditions are not excluded from this study if they present with any of the symptoms listed in the inclusion criteria. Patients who previously sought treatment for the same episode of illness in other health services (outpatient clinic in the county hospitals, etc) will be excluded, simply because the treatment sought elsewhere may bring interference or contamination to our study findings by having previously obtained antibiotics elsewhere.

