### Randomisation, allocation and blinding

All the recruited township health centres will be stratified by above or below the average baseline antibiotic prescribing rate and randomised, in blocks of 4 and 6, at a 1:1 ratio to the intervention or usual care group. Antibiotic prescribing rate (%) of each township health centre will be measured by dividing the total number of RTI patients who are prescribed antibiotics (intravenous and oral) against the total number of RTI patients who are present to each township health centre.

All participating health centres will be allocated to a trial arm at the same time, after completion of baseline data collection. Due to the nature of the intervention, it is not possible to blind practitioners to their allocation to either intervention or usual care group. However, the statisticians conducting the analysis will remain blind to allocation until quantitative analysis is complete. The trial randomisation and blinding will be conducted by an independent statistician.

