A computer-based treatment decision support system will be installed on computers in consulting rooms in the intervention clinics. This will allow practitioners to record the patient’s symptoms and the practitioner’s diagnosis and will then provide the appropriate treatment guidance from the Chinese national guidelines. The treatment decision support system has been adapted from our previous project.^27^ It contains the following sections (online supplemental appendix 5): (1) patient eligibility criteria; (2) patient symptoms: allow practitioners to record what symptoms patients are suffering from; (3) diagnosis, patient reassurance and prognosis: allow practitioners to record their diagnosis, and provide appropriate patient reassurance and prognosis for each type of RTI patient; (4) treatment recommendations for each type of RTI patient from Chinese National Guidelines for Treating Acute Respiratory Tract Infections; (5) Table of symptomatic treatment options for RTI patients (also from Chinese National Guidelines); and (6) Safety netting advice (when to come back to see the doctor) (also from the Chinese National Guidelines).

10.1136/bmjopen-2020-048267.supp5Supplementary data

Practitioners will be required to sign a public declaration letter stating that they are committed to reducing unnecessary antibiotic prescribing and display this in a public area of their clinic.

Township health centres will be provided with a leaflet that can be given to RTI patients. This leaflet will address common patient beliefs and concerns about RTI, address common misapprehensions that can lead to an expectation of antibiotic treatment, provides advice on non-antibiotic symptomatic treatment options and safety-netting.

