### Data collection methods

Baseline data will be collected for 400 patients with RTI at the participating township health centres. Follow-up data collection will be collected for 1200 patients at the participating township health centres after implementation of the intervention.

In all recruited township health centre, direct observations will be carried out by a researcher from Anhui Medical University following the doctor questionnaire (online supplemental appendix 6) adapted from our previous study.^16^ Observation will focus on the adult RTI clinical consultations and record patient symptoms, practitioner’s diagnosis & treatment, sickness severity, any antibiotics or other medicines prescribed and mode of administration (intravenous or oral), name, dosage and quantity. Immediately after the consultation, the researcher will fill in a patient questionnaire (online supplemental appendix 7) by asking questions of patients directly. This questionnaire is also adapted from the previous study^16^ and includes questions about patient demographic characteristics (gender, age, education level, residential area and medical insurance records), illness duration, symptom severity and patient satisfaction with the consultation; the latter two questions will be scored using a 10-point scale.

10.1136/bmjopen-2020-048267.supp6Supplementary data

10.1136/bmjopen-2020-048267.supp7Supplementary data

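### The entry rule contradicts itself, and as the inclusion criterion is worded the primary-outcome denominator depends on a diagnosis made after allocation by an unblinded practitioner

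*Protocol article*

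**What the plan says.** Inclusion criteria: an adult qualifies as a "Patient who is diagnosed with an RTIs in the recruitment consultation". A list of symptoms follows after a colon. The text does not say whether the list defines the diagnosis or merely illustrates it.

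Exclusion criteria: "patients with non-infective conditions are not excluded from this study if they present with any of the symptoms listed in the inclusion criteria".

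On who is approached, the section on patient recruitment states: "All patients with RTIs who seek healthcare from the recruited health centres will be screened for eligibility and invited to participate in this study". University researchers do the recruiting: "Researchers from Anhui Medical University will undertake patient recruitment on-site until 30 participants have been recruited at each township health centre".

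Timing. Under Randomisation, allocation and blinding: "All participating health centres will be allocated to a trial arm at the same time, after completion of baseline data collection". Under Data collection methods: "Follow-up data collection will be collected for 1200 patients at the participating township health centres after implementation of the intervention". The patients who supply the outcome are therefore identified once the arms are known and the intervention is running.

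Blinding: the same randomisation section says practitioners cannot be blinded. It describes masking only for the statisticians.

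Outcome: the researcher observes the consultation and records symptoms, diagnosis and prescription together. Table 1 places the primary outcome at that consultation. The denominator is RTI patients.

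Intervention: practitioners in that arm alone are trained on RTI treatment guidelines. They also use a decision aid in which they enter symptoms and a diagnosis.

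**The concern.** In a cluster trial that recruits patients after allocation, the two arms are comparable only if the same kinds of patient are identified in each. A criterion that can be met only once the practitioner has made a diagnosis puts identification in the hands of the person on whom the intervention works, at the moment of prescribing. If that person's use of the RTI label changes, the prescribing percentage can move with no change in prescribing, or a real change can be hidden.

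The planned analysis does not repair this. The clinic baseline rate is measured before allocation and carries no information on a shift that arises afterwards. Multiple imputation deals with missing values among enrolled patients, and patients who never enter are not missing data in that sense.

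The contradiction is a problem of its own. A patient with a non-infective condition and a cough has a listed symptom but no RTI diagnosis. One section admits that patient and the other does not, so field staff at 40 centres could apply different rules.

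**Working it through.** **1. The plan's own figures.** Inputs from Sample size calculation: 75% versus 60%, power 90%, alpha 0.05 (taken as two-sided), ICC 0.05, 30 patients per centre.
- Per arm before clustering, pooled variance: (1.960·√(2·0.675·0.325) + 1.282·√(0.75·0.25 + 0.60·0.40))² / 0.15² = 203. The stated 203 is reproduced.
- Design effect: 1 + 29·0.05 = 2.45. Total: 2.45·203·2 = 994.7, stated as 995.
- With 1200 recruited, the effective size per arm is 600/2.45 = 244.9, and power for 75% versus 60% is 94.6%.

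The sample size is not in question. These figures only set the scale.

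**2. Extra untreated patients in the intervention arm.** Assume 75% in both arms and no true effect. Let f be the share of enrolled intervention patients who are extra cases given no antibiotic. Observed rate = 0.75(1 − f).

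| f | Observed rate | Fall (points) |
|---|---|---|
| 5% | 71.25% | 3.8 |
| 10% | 67.5% | 7.5 |
| 20% | 60.0% | 15.0 |

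**3. Antibiotic-treated patients relabelled out of RTI.** Let g be the share of treated patients lost from the intervention denominator. Observed rate = 0.75(1 − g)/(1 − 0.75g).
- g = 10%: 0.675/0.925 = 73.0%, a fall of 2.0 points.
- g = 20%: 0.600/0.850 = 70.6%, a fall of 4.4 points.

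**4. Chance of a significant reduction with no true effect.** With n = 244.9 and d the difference between the two observed rates: Φ((d√n − 1.960·√(2p̄(1 − p̄)))/√(p₁(1 − p₁) + p₂(1 − p₂))).
- Adding untreated patients equal to 10% of the original number (f = 0.10/1.10 = 9.1%): rate 0.75/1.10 = 68.2%, chance about 39%.
- Adding 25% (f = 0.25/1.25 = 20%): rate 60.0%, chance about 95%.
- Relabelling g = 20%: rate 70.6%, chance about 19%.

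For comparison, with no shift the chance of a significant result in this direction is 2.5%.

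**5. The opposite direction.** Suppose the true intervention rate is 60% and a share s of untreated patients is no longer called RTI. Observed rate = 0.60/(1 − 0.40s).

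| s | Observed rate | Power |
|---|---|---|
| 0% | 60.0% | 95% |
| 10% | 62.5% | 85% |
| 20% | 65.2% | 66% |
| 30% | 68.2% | 39% |

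The values of f, g and s are assumptions. The article gives no figure from which any of them could be estimated.

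**The case against.** The strongest reply is that the practitioner's label may not decide entry at all. The inclusion criterion goes on to list symptoms, and the exclusion section keeps symptomatic patients whose illness is not infective. On that reading, calling a cough something other than RTI removes nobody. Researchers, not practitioners, recruit. They are in the room and record symptoms and severity, so they could apply a symptom rule and case mix could be compared by arm. This stands as an available reading. It does not stand as a settled rule: the recruitment section again speaks of patients with RTIs, and no sentence gives the symptom list precedence. Even on the symptom reading, screening and consent still follow allocation.

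A reader might also infer that the decision aid decides who enters the trial, since "It contains the following sections (online supplemental appendix 5): (1) patient eligibility criteria". The documents do not support that. The section is only named, the appendix is not shown, and nothing links it to trial enrolment. The point does not rely on it.

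That recruiters can see the arm is also an inference, though a fair one. They observe consultations, the commitment letter is on public display, and the software sits in consulting rooms. The article does not say that they are masked.

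The Data analysis section also promises adjustment for potential confounders, listed in the analysis plan. That may absorb part of a measured case-mix difference among those enrolled. It cannot bring back patients who were never identified.

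Finally, moving to a symptom rule widens the population and could separate the follow-up denominator from the baseline rate used for stratification and adjustment. That objection is sound, and the fix has to meet it.

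**Conclusion.** The point holds in this form. The inclusion and exclusion sections conflict. As the inclusion criterion is worded, membership of the primary-outcome denominator depends on a post-allocation diagnosis by an unblinded practitioner whom the intervention targets, in the consultation that yields the outcome.

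Two stronger readings should be resisted. One is that eligibility certainly turns on the practitioner's label: the exclusion wording leaves a symptom-based reading open. The other is that the trial is biased towards benefit: neither the direction nor the size of any shift can be derived from the article. The training is described as covering treatment guidelines, resistance, common concerns, use of the tool and communication, not the reclassification of illness.

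What can be said is that shifts of moderate size would matter on the trial's own scale. Under the assumptions shown, a fifth of intervention patients being extra untreated cases would reproduce the whole 15-point target, while relabelling 10% or 20% of treated patients would move the rate by 2.0 or 4.4 points. Because it concerns the primary estimate and analysis cannot recover patients never identified, the rule should be settled before follow-up recruitment.

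**What to change.** Reconcile the two sections by making the symptom rule govern, and remove the requirement for a diagnosis in the recruitment consultation.
- The on-site researcher applies the listed presenting symptoms to consecutive adults before the consultation. Those who qualify and consent count towards the 30 whatever diagnosis follows.
- The same rule is used in the baseline audit of 10 patients per centre, so that the rate used for stratification and adjustment has the same denominator as follow-up.
- The practitioner's diagnosis is recorded as a descriptive variable and reported by arm.
- Numbers screened, eligible and recruited are reported by arm.
- An analysis restricted to practitioner-diagnosed RTI is given as a sensitivity analysis.

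Cost: protocol wording and the order of steps in the field. The researchers are already on site, and the symptom list already exists. The downside is that some patients without RTI enter and may dilute the effect somewhat. The article gives no figure for how much, but its exclusion section already accepts such patients. The description of the outcome population should be brought into line with the rule.
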